## Method/design

The relevant target group for this study are adolescents aged 16 to 18 years from Belgium, the Czech Republic, Germany, and Sweden. To determine the effectiveness of the web-BI, we apply a two-arm RCT study design, with baseline assessment at study entry and a three month follow-up assessment. Figure 1 displays the trial design.

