### Assessment

Those eligible and willing to participate in the study will receive comprehensive baseline assessment questionnaires containing socio-demographic characteristics, such as age, gender, educational/vocational information, as well as their weight which will be the base for an individualised and personalised feedback in the later intervention (weight is necessary to calculate Blood-alcohol-concentration). Items concerning current substance consumption (primary outcomes) and cognitive items concerning substance use (secondary outcomes) will be assessed at baseline and follow-up. A number of potential moderator variables are included in the baseline assessment to allow for subgroup analyses. All measures are based on established scales or self-constructed according to the literature (see *Instruments* section). All assessment material will be pilot-tested for appropriateness and duration as completing the survey should not take long in order to avoid attrition.^c^

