### The control group: assessment only

The control group will receive no intervention besides the assessment. However, participants in the control group are provided with contact information on suitable counselling service providers to get in touch with in case of severe substance use-related problems. All participants are invited to visit again and participate in follow-up assessment after the evaluation period of the intervention of 3 months.

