### Instruments

#### Primary outcomes

The primary outcomes of the study refer to reductions of substance use. As prevalence rates of alcohol are particularly high among youth we distinguish measures for alcohol, which will be the main focus, from those in the broader category of drugs other than alcohol. Specifically we use the Alcohol Use Disorder Identification Test Consumption subscale (AUDIT-C) [75]) for frequency of alcohol consumption, frequency of having five drinks (four for girls) at one occasion (binge drinking), with response options ranging from 1 (*never*) to 5 (*four or more times a week*). Rather than using the third original AUDIT-C item, which measures number of standard drinks consumed per typical drinking occasion (1 = *one or two* to 5 = *ten or more*), and in order to ensure standardised responses across the four participating countries, we use a graphical overview of various types of drinks with the indication to select the number of each drink per typical drinking occasion. This way we can better account for national differences in typical standard drinks while keeping the content of the item. Standard drinks are defined as 10 g ethanol and items are assessed over the past 30 days.

For drugs other than alcohol we analogously use the first three items of the Drug Use Disorder Identification Test (DUDIT) [76] assessing frequency of consumption of drugs other than alcohol, frequency of different types of drugs other than alcohol used at the same occasion (1 = *never* to 5 = *four or more times a week*), and quantity of consumption of drugs other than alcohol on a typical consumption day (1 = *zero* to 5 = *seven or more*).

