#### Secondary measures

In addition to the behavioural outcome variables described above we assess a number of potential and theoretically plausible moderator and mediator variables, as well as several cognitive-level outcomes. Specifically, we assess the following moderators: *Age of first use*, *General Psychopathology*, using a short version of the Symptom Checklist (SCL-K 9) [79] and *Child Disclosure*[80], as an indicator of parent–child relationship quality. Positive parent–child relationship is a protective factor for adolescent substance use [81] and has been consistently shown to be related to lower likelihood of adolescent substance use [82] and variables related to adolescent substance use, such as self-control, competence, and peer affiliations [83]. Regarding potential mediators and cognitive outcomes we rely on socio-cognitive constructs based on major psychological models predicting health behaviour change, such as Ajzen’s Theory of Planned Behaviour (TPB) [84], and Prochaska & Di Clemente’s Transtheoretical Model (TTM) [85,86]. Both theories are widely used in clinical practice and health psychology and generalise across many different problem behaviours [87,88]. Specifically, we address *attitudes*, *subjective norms*, *perceived behavioural control*, and *behavioural intentions* as the proximal cognitive antecedents of goal-directed behaviour. Additionally we include a measure of *Implementation Intentions*[89] to address the action planning phase in goal attainment. Implementation intentions are defined as plans that specify the conditions under which target behaviours will be performed and help to ensure that the decision is acted upon [90]. Moreover, we include an algorithm for allocating participants into different *stages of change* concerning their substance use [91-93] hypothesising that progression (such as from precontemplation to contemplation) will be more pronounced in the intervention group compared to the control group. All items are adapted from previous related research.

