### Statistical analyses

To test the efficacy of WISEteens we address the primary research question whether participation in the intervention leads to a decrease in drinking and / or drug consumption other than alcohol at follow-up after three months compared to those adolescents in the assessment-only control group. The main analysis will follow separate analyses for alcohol and drugs. For alcohol consumption we will run multivariate analyses of covariance (MANCOVA) with intervention condition as the independent variable (intervention vs. control group) on the primary dependent variables frequency and quantity (i.e., number of drinks per typical drinking occasion) of alcohol consumption, frequency of binge drinking (AUDIT-C), reductions in weekly drinking and peak drinking. Baseline alcohol units of these variables and change scores (baseline-follow-up) of motivational (i.e., implementation intentions) and the socio-cognitive constructs (i.e., intentions, attitudes, subjective norms, PBC) based on Ajzen’s Theory of Planned Behaviour (TPB) [84] will be included as covariates. For drug use other than alcohol we will analogously run separate analyses of variance (MANCOVAs) on the primary dependent variables frequency and quantity of drug use (DUDIT-C). In addition, we will test whether socio-demographic variables (age, sex, social class), country of residence (Sweden, Germany, Belgium, Czech Republic), general psychopathology, parent–child relationship, age of first use, and stage of motivation to change moderate the outcomes. Moreover we will explore possible mediated effects of our intervention on the various behavioural measures relying on multiple mediation analysis using the syntax of Preacher and Hayes [96] for SPSS, and test direct and indirect effects in a path model using AMOS 18 [97]. Path Analysis is a multivariate technique specifying relationships between observed variables akin to running several regression equations with the advantage that it allows simultaneous testing of several propositions regarding how constructs are theoretically linked and the directionality of significant relationships within one single model [98].

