## Discussion

The present study protocol describes a two-arm RCT examining the effectiveness of a web-based brief intervention for adolescents aged 16 to 18 in four European countries. The fully electronically delivered intervention is built upon the principles of MI [22] and is explicitly designed to promote reductions in frequency and quantity of problem drinking and abstinence of drugs other than alcohol. The scope of our research questions includes theory-based analyses of the mechanisms involved in the expected behaviour change (i.e., mediators) as well as à priori specification of subgroups for differential analyses (moderators).

Internet-based brief interventions hold a number of significant advantages over traditional clinician-delivered approaches and have proven effective in addressing alcohol and drug use in the general population. Initial results concerning adolescent target groups are promising yet scarce, even more so in the field of poly-drug use. The present study will contribute to the literature on web-based interventions for this particular target group.

The present study has a number of strengths. First and foremost, our intervention is well grounded in theory incorporating elements of Motivational Interviewing and social influence which has been shown to be effective in reducing problematic substance consumption in prior research. Also, our research is guided by major psychological models of health related behaviour change, such as Ajzen’s Theory of Planned behaviour [84] and the Transtheoretical model [85]. In our study we will account for the articulated need to better understand the underlying factors of MI approaches and investigate the ways in which health behaviour may be changed to enhance effectiveness of (MI-based) interventions in promoting health [54,99]. Furthermore we are informed by the current state of the art in web-based intervention studies. For example we follow a tailored feedback approach which is likely to yield higher levels of acceptance than more static approaches especially for adolescents.

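### The path model cannot test the direction of the cognition–use link, because cognitions and consumption are measured together at one follow-up; that direction is assumed from theory

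*Protocol article*

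**What the plan says.** **Timing.** Under Method/design the trial runs "with baseline assessment at study entry and a three month follow-up assessment". Under Assessment, the consumption items and the "cognitive items concerning substance use (secondary outcomes) will be assessed at baseline and follow-up"; one sentence covers both sets. The control-group section confirms a single return visit, at which participants "participate in follow-up assessment after the evaluation period of the intervention of 3 months". For the alcohol outcome, the Primary outcomes section says that "items are assessed over the past 30 days".

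**Assumed order.** The Secondary measures section takes attitudes, subjective norms, perceived behavioural control and intentions from the Theory of Planned Behaviour "as the proximal cognitive antecedents of goal-directed behaviour".

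**Analysis.** Under Statistical analyses, mediated effects are to be explored with a multiple-mediation procedure, and direct and indirect effects are to be tested in a path model. The stated advantage of path analysis is that it allows "simultaneous testing of several propositions regarding how constructs are theoretically linked and the directionality of significant relationships within one single model". The Discussion puts "theory-based analyses of the mechanisms involved in the expected behaviour change (i.e., mediators" within the scope of the research questions. No caveat about temporal order is given.

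**The concern.** Mediation needs two links: allocation to cognition, and cognition to use. Randomisation gives the first a direction. It does nothing for the second, where only measurement order or outside knowledge can help. Here the measurement order does not help, and for the alcohol items it runs the wrong way: the follow-up cognition is recorded at the end of the 30 days that the outcome describes. Baseline cognitions do precede the outcome, but they also precede randomisation and so cannot carry an intervention effect.

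Adolescents who drink less for any reason may then come to report less favourable attitudes to drinking. The planned analysis would count that as mediation by attitudes. With the directionality sentence in place, a reader of the results could take the fitted arrows as a finding about how the intervention works.

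**Working it through.** **Step 1. Can fit tell the two orders apart?** Let T be allocation, M the follow-up cognition, Y follow-up use and B the baseline measures. Because the plan tests both direct and indirect effects, the direct path from T to Y stays in the model. For one mediator the two orders are then two factorisations of the same joint distribution:

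f(M | T, B) × f(Y | M, T, B) = f(Y | T, B) × f(M | Y, T, B).

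Their likelihoods are identical. In 2,000 simulated data sets for each of eight settings, the largest log-likelihood difference was below 1e-12.

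**Step 2. How large is the false indirect effect?** The article gives no cognition–use association, so the values below are assumptions. The arm effect of 0.2 SD is the effect size in the Sample size section. Suppose use drives cognition and true mediation is zero:

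- Y = −0.2T + e, with Var(e) = 1
- M = gY + u, with Var(u) = s²

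Fitting the planned order gives a = −0.2g and b = g / (g² + s²). The share falsely shown as mediated is ab / (−0.2) = g² / (g² + s²), which is the squared within-arm correlation of M and Y.

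- g = −0.5, s² = 0.75 (r = 0.5 in size): a = 0.10, b = −0.5, ab = −0.05, share 0.05 / 0.20 = 25%. A simulation of 4,000 trials with 200 per arm gave −0.050 for the indirect effect and −0.149 for the direct effect.
- g = −0.5, s² = 1: b = −0.5 / 1.25 = −0.4, ab = −0.04, share 20%.
- r = 0.3 in size: share 0.3² = 9%.

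**Step 3. Does baseline adjustment remove it?** Now let Y = 0.5Y₀ − dT + e with Var(e) = 0.75, and M = 0.5M₀ + gY + u with Var(u) = 0.75 − g². Given allocation and both baselines, the share is 0.75g² / (0.75g² + 0.75 − g²):

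- g = −0.3: 0.0675 / 0.7275 = 9%
- g = −0.5: 0.1875 / 0.6875 = 27%

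It does not. The table shows 2,000 runs per row, with a Monte Carlo 95% interval for the indirect effect. The size 400 per arm is the recruitment target; 200 is what remains after the article's worst-case 50% loss.

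| Per arm | Arm effect d (SD) | g | Falsely mediated share | Runs with a significant false indirect effect |
|---|---|---|---|---|
| 200 | 0.2 | −0.3 | 9% | 10% |
| 200 | 0.2 | −0.5 | 27% | 24% |
| 200 | 0.4 | −0.3 | 9% | 28% |
| 200 | 0.4 | −0.5 | 28% | 67% |
| 400 | 0.2 | −0.3 | 9% | 17% |
| 400 | 0.2 | −0.5 | 28% | 40% |
| 400 | 0.4 | −0.3 | 9% | 53% |
| 400 | 0.4 | −0.5 | 27% | 93% |

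The nominal rate is 5%. At the article's own effect size of 0.2, most runs show no significant false mediation, but the rate is still 2 to 8 times nominal.

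**The case against.** The strongest reply is that the article claims less than this. It speaks of exploring mediation, lists mediators under secondary research questions and calls them potential. The directionality sentence describes path analysis in general and cites a reference. The causal order is openly borrowed from an established theory, which is ordinary practice in exploratory mediation. The primary comparison does not need the path model. Model covariates, reverse-order fits and sensitivity analyses normally belong in a full analysis plan, which is not shown.

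Much of this stands, and it rules out stronger readings that a reader might infer:

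- That the plan promises to reveal mechanisms. It does not; the Discussion names them as a research question.
- That mechanism is the leading strength claimed. The Discussion gives first place to the intervention's theoretical grounding; understanding underlying factors comes later in that paragraph.
- That mediation is presented as confirmatory. The article already calls it exploration, although it also speaks of testing direct and indirect effects.
- That leaving out sensitivity analyses is itself an error. In a condensed article it is not.

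What does not stand is that these points cure the sentence. It is offered as the advantage of the method chosen for this trial, without a caveat, and the design lacks that property. An exploratory label does not make an unidentified direction testable.

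A more technical reply is that an over-identified path model, with some paths left out, can fit better in one order than the other. That comparison tests the omitted paths jointly with the order. Dropping the direct path, for example, assumes that cognition carries the whole effect, which the plan does not assume.

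**Conclusion.** The point holds as a limit on what may be concluded from a secondary, exploratory analysis. The timing facts and the equivalence of the two orders rest on the article and on algebra. The direction of the cognition–use path is assumed and cannot be tested with these data.

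The size is illustrative. With reverse causation only and true mediation zero, roughly 10% to 25% of the total effect would appear mediated for assumed correlations of about 0.3 to 0.5. The figure is essentially the assumed correlation squared, so it should not be read as an estimate for this trial.

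Nor should the point be read as casting doubt on the efficacy result. The between-arm comparison does not use this path model. The separate use of cognitive change scores as MANCOVA covariates is a different question and is not judged here.

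**What to change.** 1. Delete the statement that the path analysis tests directionality.
2. State that indirect effects are associational, that the order from cognition to use is assumed from theory, and that no conclusion about mechanism will be drawn from them alone.
3. Adjust both the mediator model and the outcome model for baseline cognition and baseline consumption. This deals with confounding by those measures; as shown above, it does not settle direction.
4. Report the reverse-order model (allocation to consumption to cognition) beside the planned one, to show readers that the data do not distinguish the orders. It should not serve as a fit test: with all paths included both orders always fit equally well, so a rule based on whether both fit would decide nothing.
5. Add a sensitivity analysis for unmeasured confounding of the mediator–outcome link.

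Items 3 to 5 may already be in a fuller plan; if so, only the wording changes. No new data are needed. The cost is a weaker mechanistic claim and slightly more analysis.

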## Discussion

The present study protocol describes a two-arm RCT examining the effectiveness of a web-based brief intervention for adolescents aged 16 to 18 in four European countries. The fully electronically delivered intervention is built upon the principles of MI [22] and is explicitly designed to promote reductions in frequency and quantity of problem drinking and abstinence of drugs other than alcohol. The scope of our research questions includes theory-based analyses of the mechanisms involved in the expected behaviour change (i.e., mediators) as well as à priori specification of subgroups for differential analyses (moderators).

Internet-based brief interventions hold a number of significant advantages over traditional clinician-delivered approaches and have proven effective in addressing alcohol and drug use in the general population. Initial results concerning adolescent target groups are promising yet scarce, even more so in the field of poly-drug use. The present study will contribute to the literature on web-based interventions for this particular target group.

The present study has a number of strengths. First and foremost, our intervention is well grounded in theory incorporating elements of Motivational Interviewing and social influence which has been shown to be effective in reducing problematic substance consumption in prior research. Also, our research is guided by major psychological models of health related behaviour change, such as Ajzen’s Theory of Planned behaviour [84] and the Transtheoretical model [85]. In our study we will account for the articulated need to better understand the underlying factors of MI approaches and investigate the ways in which health behaviour may be changed to enhance effectiveness of (MI-based) interventions in promoting health [54,99]. Furthermore we are informed by the current state of the art in web-based intervention studies. For example we follow a tailored feedback approach which is likely to yield higher levels of acceptance than more static approaches especially for adolescents.

Among the limited amount of studies using adolescent samples to our knowledge we are the first to design and test a brief intervention for poly-drug using adolescents in a fully-electronic format. Another strong aspect of the present trial is its multi-centre approach with collected data from four European countries, allowing for international comparisons. Finally, we consider it strength to rely solely on internet recruitment in our target population. This approach matches real conditions and directly tests the external validity of our website should its effectiveness be proven. Note that this procedure deviates from other studies which typically test offline before going online [28,55]. While failure to retain a sufficient proportion of participants for follow-up assessment remains a concern for the evaluation we consider it vital to develop a web-site that will be accepted by our target group.

## Conclusions

In this study protocol, we described a research project for testing an intervention aimed at reducing drinking and promoting abstinence from illicit drugs among adolescents in four European countries. Evaluation of the intervention will provide insights into the effectiveness of web-based screening and brief intervention for poly-drug use among adolescents aged 16 to 18 years in Europe.

## Endnotes

^a^CRAFFT represents an acronym of the first letters of the key words addressed in the test’s six items (Car, Relax, Alone, Forget, Friends, Trouble).

^b^As a part of this participants will be encouraged to create a new e-mail address, one that does not contain their name.

^c^Note that the amount of assessment tools necessary for this evaluation study exceeds the amount of items necessary for running the later internet version of the intervention, and will be removed after the evaluation phase of the project.

^d^Note that we focus particularly on drinking. Nevertheless, participants will be encouraged throughout the intervention to take the exercises as templates for use of other substances.

^e^Because of large heterogeneity in the format of the national prevalence data we decided to use the Swedish representative national AUDIT-C scores as the basis for normative comparisons.
